## Abstract

**Background:**

Polycystic ovary syndrome (PCOS) is one of the most frequent endocrine disorders among women of fertile age. Women with PCOS manifest clinical symptoms like menstrual dysfunction, hirsutism, insulin resistance, and hyperinsulinemia. As excessive amounts of insulin levels directly increase ovarian production of androgens, hyperinsulinemia and insulin resistance are considered as the pathogenesis factors of PCOS. The portfolio low-carbohydrate diet (PLCD) is a plant-based diet with 40% carbohydrates combined with five cholesterol-lowering foods and nutrients. On the other hand, the ketogenic diet (KD) is a nutritional protocol with 10% carbohydrates. The purpose of this study is to determine whether PLCD or KD is more effective in alleviating PCOS symptoms.

**Methods:**

Forty-six overweight or obese women diagnosed with PCOS will be randomly stratified to receive either PLCD or KD for 8 weeks. Measures related to anthropometric and body composition, glucose, and insulin level, HOMA-IR, sex hormones, lipid profile, quality of life, dietary intake, physical activity, and Ferriman-Gallwey score of all participants will be accessed before and after the intervention.

**Discussion:**

Since the first line treatment of PCOS is lifestyle adjustment including diet control and exercise, there has not been determined the optimal diet for this population of women yet. Hence, the goal of conducting this study is to determine whether the PLCD or the KD could have more advantageous effects on attenuating PCOS manifestations. The result of this investigation will give us new insight into curing this disease and will provide evidence-based recommendations for prescribing an optimal diet for PCOS women.

**Trial registration:**

IRCT20200912048693N3, Trial registered 2022–12-14.

https://www.irct.ir/trial/67548

## Introduction

### Background and rationale {6a}

Polycystic ovary syndrome (PCOS) is the most common endocrine–metabolic disorder, with a prevalence of 4–20% depending on the diagnostic criteria used, among reproductive-aged women [1]. The clinical manifestations of PCOS include menstrual disturbances like oligomenorrhea, amenorrhea, prolonged irregular menstrual bleeding, and signs of androgen excess such as hirsutism and acne as well as alopecia [2]. A diagnosis of PCOS is when at least two of three Rotterdam criteria are presented: (i) clinical hyperandrogenism (such as hirsutism, acne, seborrhea, and alopecia) and/or high circulating androgens levels; (ii) presence of ovarian cysts assessed by ultrasound examination; and (iii) oligo-amenorrhea with oligo-anovulation [3]. Based on these three key parameters of PCOS, four phenotype classifications have been identified [4] (Table 1). As it is illustrated, phenotype A is the most severe, while phenotype D is the least one along an axis of metabolic and ovarian dysfunction. According to a study, phenotypes A, B, and C are endocrine-metabolic syndromes, while phenotype D is non-hyperandrogenic PCOS which represents evidence of both oligo-anovulation and ovarian cysts [5].

**Table 1 Tab1:** Four phenotype classifications of PCOS according to Rotterdam criteria. As it has shown, phenotype A (classic PCOS) represent all manifestations of PCOS and is the most severe type, whereas phenotype D (non-hyperandrogenism PCOS) manifest neither hyperandrogenism, nor insulin resistance

Features	Phenotype A	Phenotype B	Phenotype C	Phenotype D
Clinical hyperandrogenism	✔	✔	✔	✗
Presence of ovarian cysts	✔	✗	✔	✔
Oligo- or anovulation	✔	✔	✗	✔

✔: Feature present

✘: Feature absent

Despite its etiology is not completely understood, studies indicate that genetic, environmental, metabolic, and endocrine factors all contribute to the pathogenesis of PCOS [6]. Environmental factors are related to both obesity and lifestyle habits [7], while endocrine contributor associated with insulin resistance and hyperinsulinemia [8]. However, approximately 75% of PCOS patients are overweight and/or obese; central obesity is observed in both normal and overweight women [9]. Furthermore, central obesity led to the progression of metabolic syndrome, defined as a tendency of hyperinsulinemia, insulin resistance, and dyslipidemia [10]. Excessive insulin production is directly related to the increased ovarian production of androgens and PCOS manifestations [11]. Women with PCOS also indicate an atherogenic lipid profile, with elevated levels of low-density lipoprotein, cholesterol, and triglycerides, accompany by reduced levels of high-density lipoprotein [12]. Although there has not been a certain treatment for this disease, lifestyle modification, such as diet and exercise, is recommended as the first-line therapy for women with PCOS [13]. Studies demonstrated a 5–10% weight reduction will not only reduce insulin and testosterone levels but also improve ovulatory function and pregnancy rates [14].

The portfolio low-carbohydrate diet is a plant-based diet with 40% carbohydrate, 20% protein, and 40% fat. The Portfolio diet was developed in the early 2000s as a “portfolio” of five cholesterol-lowering foods and nutrients (plant protein, viscous fiber, nuts, and phytosterols) [15]. The Portfolio diet has lower saturated fat and cholesterol with five food components added to the diet, including plant protein from soy products or dietary pulses, viscous soluble fiber from oats, barley, certain fruits, nuts, and plant-based monounsaturated fats (MUFAs) in forms of olive and canola. Studies indicate that the Portfolio diet has positive effects on lipid profile and increase high-density lipoprotein (HDL) cholesterol [16]. On the other hand, studies confirm that following a low carbohydrate diet indicates improvements in waist circumference, fasting glucose and, serum insulin as well as weight in women with polycystic ovary syndrome [17]. In this way, Thomson and colleagues indicated that a low carbohydrate diet with 30% protein, 40% carbohydrate, and 30% fat on 94 overweight and obese women with PCOS during 20 weeks could decrease fat mass and fat-free mass 3 and 2 kg, respectively [18]. The ketogenic diet is a nutrition protocol of high-fat (70–80%), very low-carbohydrate (5–10%) diet which represent beneficial effects in a number of diseases, including obesity, neurological disorders, type 2 diabetes mellitus, cancer, and PCOS [19, 20]. The role of a ketogenic diet on PCOS is through the reduction of the amount of circulating glucose and insulin, which results in both declining glucose oxidation and increasing fat oxidation [21]. While many studies illustrate, KD significantly decreased body weight, glucose, and insulin levels, triglycerides, total cholesterol, LH, testosterone, and DHEA levels with a significant improvement of HOMA-IR. Furthermore, estradiol, progesterone, SHBG, and HDL increased [22, 23].

Despite there not being indicated a certain diet for PCOS therapy [24], studies revealed low-carbohydrate diets are more effective than standard hypocaloric diets, due to their regulatory effects on insulin secretion [17]. For instance, in 2022, a clinical trial was conducted to determine the therapeutic effects of the Mediterranean low-carbohydrate diet (MED/LC) (20% of carbohydrate) with a low-fat diet (30% fat) in 72 overweight PCOS patients for 12 weeks. Their results illustrated that the MED/LC was more effective in modifying anthropometric parameters, reproductive endocrine levels, insulin resistance levels, and lipid levels compared with the low-fat diet and recommended the MED/LC diet for the treatment of overweight patients with PCOS [25]. Another investigation through 14 overweight PCOS women revealed a significant reduction of anthropometric indices, insulin, glucose level, HOMA-IR, and lipid profile, as well as reproductive endocrine hormones after following a ketogenic diet. It also considered the KD as a valuable non pharmacological treatment for PCOS patients [21].

As it has been shown, studies have confirmed the positive effect of both low-carbohydrate and ketogenic diets on PCOS because of their lower amount of carbohydrates and the consequence of lower levels of insulin secretion in comparison with the conventional diet. Consequently, these two diets could effectively reduce hyperandrogenism as well, which could be beneficial for patients with phenotypes A, B, and C of PCOS. However, for phenotype D, which lacks hyperandrogenism, these dietary interventions do not hold therapeutic rationale due to the distinct etiology. Overall, due to our knowledge, there has not been any study to represent which of these two diets is more effective on treating PCOS. Therefore, the aim of the present study is to determine whether the PLCD or the KD could have more beneficial effects for improving PCOS by measuring anthropometric indices, hormonal status, lipid profile, quality of life, dietary intake, physical activity, and Ferriman-Gallwey score.

### Objectives {7}

To determine the effect of PLCD compared to the KD on anthropometric (height, weight, waist circumference, hip circumference, waist-to-hip ratio, and body mass index), body composition indices (fat body mass, lean body mass), and basal metabolic rate (BMR) in overweight and obese women with PCOSTo determine the effect of PLCD compared to the KD on the sex hormonal (LH, FSH, DHEA) status in overweight and obese women with PCOSTo determine the effect of PLCD compared to the KD on hirsutism status in overweight and obese women with PCOSTo determine the effect of PLCD compared to the KD on lipid profile in overweight and obese women with PCOSTo determine the effect of PLCD compared to the KD on insulin, and glucose level, as well as HOMA-IR in overweight and obese women with PCOSTo determine the effect of PLCD compared to the KD on the quality of life in overweight and obese women with PCOS

### Trial design {8}

This is a parallel-arm, open, stratified randomized clinical trial. Forty-six overweight or obese women diagnosed with PCOS will be randomly stratified to receive either PLCD or KD for 8 weeks.

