## Assignment of interventions: allocation

### Sequence generation {16a}

#### Randomization

During the first visit, participants will be randomized to either the PLCD or the KD. Randomization will be conducted by an investigator who is not involved in obtaining or entering participants’ data. The samples will be included in the study with informed consent using a random block method of 6 that will be created by the website https://www.sealedenvelope.com.

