#### Concealment mechanism {16b}

The following will be considered in the implementation of the random assignment process: (a) one English letter is assigned to each of the groups: A to the PLCD group, B to the KD group; (b) a sequence for the sample size 23 will be created; (c) for the concealment process of random allocation, 23 non-transparent envelopes and cards (as much as the total sample size) will be prepared. Inside each envelope, 6 cards will be placed in the order of the sequence in each block. Block numbers will be written on each envelope. The name of the desired group will be written on each card in sequence.

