#### Implementation {16c}

The investigator who collects the information is unaware of the type of allocation of the samples to the study groups. The participants will be enrolled to the study by both a dietitian and an obstetrician-gynecologist according to the eligible criteria. Then, the dietitian will randomly stratified participants to receive either PLCD or KD.

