### Methods for additional analyses (e.g., subgroup analyses) {20b}

We intend to perform subgroup analysis, such as fat body mass vs. lean body mass, LDL vs. HDL, testosterone vs. luteinizing hormone (LH). We will try to match for most variables across groups. Adjustments will be made for confounding factors like waist circumference, macronutrients consumption, and physical activity.

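### The trial is labelled stratified but its stated allocation has no strata; the matching sentence should go, and the envelope procedure leaves an open allocation predictable

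*Protocol article*

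**What the plan says.** **Label.** Trial design {8} states: "This is a parallel-arm, open, stratified randomized clinical trial". Study setting {9} repeats it. Elsewhere the verb is used loosely for *allocate*: women "will be randomly stratified to receive either PLCD or KD for 8 weeks" (Trial design; similar wording in the Abstract and under choice of comparators), and "the dietitian will randomly stratified participants to receive either PLCD or KD" (Implementation {16c}).

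**Method.** Sequence generation {16a} includes women "using a random block method of 6 that will be created by the website". Concealment mechanism {16b} says "a sequence for the sample size 23 will be created" and "23 non-transparent envelopes and cards (as much as the total sample size) will be prepared". It continues: "Inside each envelope, 6 cards will be placed in the order of the sequence in each block". Envelopes are marked with the block number. No section names a stratification factor, its levels or separate lists.

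**Who allocates.** Sequence generation gives randomisation to an investigator with no part in obtaining or entering participant data. Implementation has the dietitian and the obstetrician-gynecologist enrol, and the dietitian then allocate. Blinding {17a} says there is none.

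**Analysis.** Statistical methods {20a} gives a diet-by-time repeated-measures ANOVA, without a stratum term. Additional analyses {20b} says "We will try to match for most variables across groups" and, in the next sentence, promises adjustment for confounders. Section {20c} commits to intention to treat.

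**The concern.** A stratified trial is one whose allocation list is built separately within levels of a named baseline factor. Readers who meet that word will credit the trial with balance on some prognostic factor. Blocks alone balance only the head-count.

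The matching sentence raises a different issue. In a two-arm parallel trial, balance on baseline variables comes from chance or from a pre-specified restriction on the sequence. If no such restriction exists and staff nonetheless try to match the groups, judgement enters either the choice of arm or the choice of who is analysed.

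A third issue stands apart from both: whether the person deciding on a woman's enrolment can foresee her arm. That depends on the block size, the envelopes, the lack of blinding and who holds the allocation.

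**Working it through.** The plan states no figure on this point, so there is none to reproduce.

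**1. Label against method.** A stratified design needs a factor, its levels, one list per level and, normally, the factor in the model. The article gives one sequence, one block size and envelopes identified by block number, with no stratum term in {20a}. The first three requirements are contradicted by the procedure it sets out. The missing model term only supports this, since an analysis plan could add one.

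**2. Possible meanings of the matching sentence.**
- Covariate adjustment: the next sentence covers that separately.
- Stratified or covariate-balancing allocation: legitimate, but no such procedure is described.
- Choosing the arm to even out the groups: overrides chance.
- Selecting women afterwards: drops randomised participants, against {20c}.

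None of these makes the sentence a usable instruction as it stands.

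**3. Predictability of fixed blocks of 6 (3:3) in an open trial.** Assume the observer knows the block size and past allocations, and guesses the arm with more cards left.
- Chance that positions 1 to 6 are already determined: 0, 0, 0, 0.1, 0.4, 1. Sum 1.5 of 6 (25%).
- Chance of a correct guess at positions 1 to 6: 0.5, 0.6, 0.6, 0.7, 0.7, 1. Sum 4.1 of 6 (68%).
- For 46 women (7 full blocks plus 4): determined 7 × 1.5 + 0.1 = 10.6 (23%); guessed correctly 7 × 4.1 + 2.4 = 31.1 (68%), against 23 by tossing a coin.
- If whoever opens a block envelope sees all six cards, the other five are disclosed: up to 7 × 5 + 3 = 38 of 46 known in advance.

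**4. Chance imbalance without strata, 23 v 23.**
- Standard error of a difference in baseline means: SD × √(2/23) = 0.29 SD.
- P(gap > 0.5 SD) = P(|Z| > 0.5/0.295 = 1.70) ≈ 0.09 for any one variable.
- For a binary factor with an assumed prevalence of 30% to 50% (not in the article), the hypergeometric probability of a gap of 20 percentage points or more is about 0.11 to 0.24.

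**5. Envelope count.** The article's total is 46, with 23 per arm. Concealment calls 23 the total. Blocks of 6 need 46/6 = 7.67, so 8 envelopes; 23 envelopes of 6 cards would make 138 cards.

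**The case against.** Several counter-arguments have force.

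- **This is a language slip.** In most places *stratify* plainly means *allocate*, and no section promises balance on a named factor. That is largely right. But Trial design and Study setting use the word as a formal design label, and there it is wrong as written. The flow diagram is not shown and the article is condensed, so strata cannot be excluded absolutely. Yet the allocation procedure is set out in some detail and gives no sign of them.
- **The matching sentence is tentative and sits under additional analyses.** True. The documents do not say that women will be exchanged, replaced or steered. The criticism is conditional on the sentence being acted on.
- **Safeguards exist.** The envelopes are opaque, and an uninvolved investigator is named. That investigator may only generate the list while the dietitian opens envelopes. Even on that reading, an enrolling person handles an envelope holding a whole block.
- **Unstratified blocks are valid for 46 women.** Agreed. Stratifying is an option, not a requirement.

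Two stronger inferences are tempting and should not be drawn. First, a reader might infer that the missing strata are what allows steering. They are not: strata with the same fixed blocks and envelopes would leave the exposure unchanged. Second, a reader might set a chance gap in baseline weight against the planned difference in weight change and call the result bias. These are different quantities. The outcome is change before to after, so a baseline gap largely subtracts out, and chance imbalance is random error already reflected in the test's standard error.

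**Conclusion.** The concern holds in three limited parts.

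1. The article claims stratification that its stated method does not deliver. The fault is certain from the text. Its consequence is mainly that readers will be misled about the design.
2. The matching sentence describes something block randomisation cannot do. It would damage the randomised comparison and the intention-to-treat analysis only if acted on.
3. Allocation is open to prediction: about a quarter of assignments certain and about two thirds guessable, for someone who knows the block size and the past allocations, and more if a whole block of cards is seen at once. The text shows that steering is possible, not that it will happen.

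The imbalance figures in the working describe what an unstratified list of this size does by chance. They are no estimate of bias in the primary result.

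**What to change.** **Label.** Choose one:
- Generate one blocked list per level of a factor known at screening, for example BMI 25–29.9 v ≥ 30 kg/m², and include that factor in the primary model; or
- Remove *stratified* wherever it describes the design or the act of allocation, and call the trial block-randomised. This resolves the contradiction fully. If enrolment has already begun on a single list, it is the only option left.

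**In either case:**
- Delete the matching sentence and state that no matching, exchange or replacement of women follows allocation.
- Reconcile Sequence generation with Implementation, so that someone not involved in enrolment holds and opens the allocation. Study setting places allocation after the baseline blood tests and Sequence generation places it at the first visit; settle that as well.
- Use one sealed, opaque, numbered envelope per woman, and preferably varying block sizes unknown to those who enrol. Single envelopes alone do not stop inference from a known fixed block size.
- Correct the sequence length and envelope count from 23 to the full 46.

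**Cost.** Mostly wording and envelopes. Strata need a second list and can leave arm sizes slightly unequal. With 46 women and two lists in blocks of 6, the worst case is a difference of 4 (for example 3 from one incomplete block and 1 from the other), that is 25 v 21. A single list can already end at 24 v 22, since the four women in the last block split 3:1 with probability 0.2 + 0.2 = 0.4.

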## Methods: participants, interventions, and outcomes

### Study setting {9}

This is a parallel-arm, open, stratified randomized clinical trial. The protocol was approved by the Medical University of Kermanshah Research Ethics Board (IR.KUMS.REC.1401.404). Furthermore, the trial was registered on irct.ir (IRCT20200912048693N3) on 2022 December 14. This study will be conducted in Fatahi Clinic of Kermanshah, Iran. As the study design is detailed in Fig. 1, potential patients firstly will be invited to Fatahi Clinic where a registered dietitian (RD) and an obstetrician-gynecologist will visit them to assess whether they have eligibility to enter this trial. Also, participants will provide written informed consent after the study was fully explained. Then, desirable participants will return to the Reference Laboratory of Kermanshah to undergo baseline blood tests including FBS, insulin level, and lipid profile, as well as sex hormones during the beginning of the follicular phase (days 3–8 of the menstrual cycle). After that, women will return to the Fatahi Clinic to have a dietary consult with an expert dietitian and randomly receive one of the diets. They will also be encouraged to return 2 months later to determine dietary adherence and undergo end of intervention testing. During these 2 months, the dietitian will call each patient every 2 weeks to follow-up with them and, if necessary, provide them with appropriate recommendations.

**Fig.1 Fig1:**
[figure not shown]
CONSORT flow diagram of study design for portfolio low-carbohydrate and the ketogenic diet in women with polycystic ovary syndrome

### Eligibility criteria {10}

#### Inclusion criteria

The inclusion criteria are as follows:Written informed consentDiagnosis with PCOS according to the Rotterdam Criteria by an obstetrician-gynecologistAge 18–45 yearsBMI ≥ 25 kg/m^2^

#### Exclusion criteria

The exclusion criteria are as follows:Currently pregnancy or lactationTaking anti-psychotic or anti-seizure medication due to their induce effect on insulin resistanceFollowing a specific nutritional diet or hypocaloric diet in the last 3 monthsHistory of diabetes or other endocrine disorders (thyroid dysfunction and adrenal disorders)Using medications that impact carbohydrate or lipid metabolism (oral contraceptive pills, antiepileptic, antipsychotics, statins, and fish oil)Using fertility-enhancing or weight loss medications (except metformin)History of hormonal therapy and/or insulin-sensitizers within the previous 2 monthsHistory of hepatic and renal disorders, hypertension, diagnosed anemia, severe respiratory disease (asthma and chronic bronchitis), and heart disease

### Who will take informed consent? {26a}

The data of all of the participants will be kept in the Kermanshah University, and just investigators of this trial will have access to them.

### Additional consent provisions for collection and use of participant data and biological specimens {26b}

On the consent form, participants will be asked if they agree to use their data should they choose to withdraw from the trial. Participants will also be asked for permission for the research team to share relevant data with people from the universities taking part in the research or from regulatory authorities, where relevant. This trial does not involve collecting biological specimens for storage.

